### Participant Selection

Children attending preschools in Mangalore Taluk aged from 24 to 72 months are included. Additional inclusion criteria are as follows: at least one soft caries lesion (ie, cavitated active caries lesion) that is small (less than half of the mesial or distal or less than one-third of the buccal, lingual, or occlusal surfaces). The exclusion criteria are pulpal exposure, history of pain, nonvital teeth, swelling or fistula, silver allergy, arrested caries or inactive lesions, teeth at the period of shedding, restored teeth, secondary caries, fluorosis, enamel hypoplasia, uncooperative behavior, physical or mental disability, and a lack of signed informed consent.

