### Baseline and Follow-up Oral Examinations

Before conducting the trial, the principal investigator was trained and calibrated by experienced dental public health specialists in the Caries Assessment Spectrum and Treatment (CAST) index. Training and calibration sessions included theoretical aspects and were followed by clinical examination of a group of 10 subjects from the outpatient department. The subjects were reexamined by the principal investigator and the guide (an experienced dental public health specialist) after 1 week. The κ coefficient values for intraexaminer and interexaminer reliability were 0.88 and 0.80, respectively, reflecting a high degree of conformity in the observations.

The examinations in this study are performed by a single examiner with the help of a recording device in preschools in Mangaluru Taluk. The study sample comprises 3 groups of children aged 24 to 72 months. After baseline examination, eligible children are randomly allocated to 1 of the 3 groups using the lottery method. Group 1 receives 12% SDF semiannually, group 2 receives 30% SDF semiannually, and group 3 receives 38% SDF semiannually. Dental caries will be measured using the CAST index [9].

A CAST score of 0 is given to sound teeth (ie, with no visible evidence of a distinct carious lesion); a score of 1 for pits or fissures that are at least partially covered with a sealant material; a score of 2 for cavities that have been restored with a direct or indirect restorative material; a score of 3 for distinct visual change in the enamel only or clearly visible caries-related discoloration, with or without localized enamel breakdown; a score of 4 for internal caries-related discoloration in the dentine, with the discolored dentine visible through the enamel, which may or may not exhibit a visible localized breakdown; a score of 5 for distinct cavitation into the dentine with the pulp chamber showing intact pulp; a score of 6 for involvement of the pulp chamber with distinct cavitation reaching the pulp chamber or with the presence of only root fragments and abscess or fistula; a score of 7 for pus-containing swelling or a pus-releasing sinus tract related to a tooth with pulpal involvement; a score of 8 for teeth that have been removed because of dental caries; and a score of 9 for teeth that do not match any of the above descriptions.

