All tooth surfaces, including the buccal, lingual, mesial, distal, and occlusal surfaces for posterior teeth, are evaluated for caries. Miller’s criterion is used to assess whether active caries are present; Miller’s criterion suggests that a carious lesion is termed active if a blunt University of North Carolina–15 probe can easily enter it; a carious lesion is defined as halted when the dentine cannot be penetrated.

The size of the lesion is categorized as small or large at the tooth-surface level (less than one-third of the buccal, lingual, or occlusal surface, or less than half of the mesial or distal surface).

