### Effect Modification

A parental questionnaire is administered at baseline regarding the children’s oral hygiene habits (eg, tooth brushing), fluoride agent use (eg, fluoride toothpaste), dietary habits (eg, bottle feeding), and source of drinking water.

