### Statistical Analysis

Data analysis will be done using SPSS (version 23.0; IBM Corp). Continuous variables will be presented as the mean (SD). Categorical variables will be presented as frequencies and percentages. To confirm normality, the Shapiro-Wilk and Kolmogorov-Smirnov tests will be used. A one-way analysis of variance (ANOVA) statistical test will be used to compare the means of continuous outcome variables if the data follow a normal distribution. Nonparametric tests (ie, the Kruskal-Wallis statistical test) will be used in the data analysis in cases when there is skewed distribution of data. Post hoc tests will be performed with an ANOVA or the Kruskal-Wallis test.

Binary logistic regression will be performed. The dependent variable will be whether the lesion is arrested or not at the 12-month examination, and the independent variables will include the children’s oral hygiene habits (eg, tooth brushing), fluoride agent use (eg, fluoride toothpaste), dietary habits (eg, bottle feeding), and source of drinking water.

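### The logistic model for 12-month caries arrest names only parent-reported habits: study group and the baseline lesion and caries measures the trial records are not named

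*Protocol article*

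**What the plan says.** The Outcome Measure section makes caries arrest at month 12 primary. The Statistical Analysis section assigns ANOVA or Kruskal-Wallis to continuous outcomes and describes categorical variables by frequencies and percentages. It then adds "Binary logistic regression will be performed". Of that model it says: "The dependent variable will be whether the lesion is arrested or not at the 12-month examination, and the independent variables will include the". Four entries then make up the list, and none of them is a treatment or lesion variable: "oral hygiene habits (eg, tooth brushing), fluoride agent use (eg, fluoride toothpaste), dietary habits (eg, bottle feeding), and source of drinking water".

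All four domains come from one source, described under Effect Modification: "A parental questionnaire is administered at baseline regarding the" same topics.

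The section on baseline and follow-up oral examinations describes other data:
- caries status: "Dental caries will be measured using the CAST index"
- site: "All tooth surfaces, including the buccal, lingual, mesial, distal, and occlusal surfaces for posterior teeth, are evaluated for caries"
- size: "The size of the lesion is categorized as small or large at the tooth-surface level"

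Participant Selection requires "at least one soft caries lesion (ie, cavitated active caries lesion) that is small", and excludes pulpal exposure, nonvital teeth, restored teeth and arrested lesions.

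**The concern.** The trial exists to compare three concentrations on arrest. The one model named for that outcome does not name the concentration, so as written it estimates associations between habits and arrest and no treatment contrast.

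The covariates it does name are parent-reported behaviours. The features of the lesion and mouth that the examiner records are not named. Allocation is by lottery, and no stratification by lesion feature is described, so the analysis is the only place left to account for chance differences in site or caries burden between arms.

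At stake are a clearly defined primary comparison and a modest amount of power in a trial planned for 40 evaluable children per arm.

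**Working it through.** **1. Model against data collected**

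| Item | Recorded? | Named in the arrest model? |
|---|---|---|
| Study group | yes (allocation) | no |
| Oral hygiene, fluoride use, diet, water source | yes (questionnaire) | yes |
| Tooth surface | yes (examination) | no |
| CAST score | yes (examination) | no |
| Lesion size, small or large | yes (examination) | no |

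**2. Which lesion measures can vary.** The qualifying lesion must be small, cavitated and active, without pulpal exposure. If one qualifying lesion per child is analysed, size is constant and adjusting for it gains nothing. Its CAST score is also confined to a narrow part of the 0 to 9 scale. Tooth surface and the child's overall caries burden can vary. Size varies only if further lesions are analysed. Eligibility asks for at least one small lesion and does not rule out others.

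**3. The plan's own sample size.** Inputs from Sample Size Estimation are alpha 5%, power 80%, effect size 0.63 and drop-out 20%. Two-sidedness, and reading 0.63 as a pairwise standardized difference, are my assumptions because the article states neither.

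n per arm = 2 × ((1.960 + 0.842) / 0.63)² = 39.6, rounded up to 40. Then 3 × 40 = 120, and 120 / 0.8 = 150. Both stated totals reproduce. The calculation uses no covariate, so nothing here changes the stated sample size.

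**4. Value of a baseline covariate.** The article gives neither expected arrest rates nor the strength of any baseline predictor, so both are assumed. The simulation has 3 × 40 children with one lesion each, and a logistic model with arm plus four non-prognostic habit variables, fitted with and without one standardized baseline covariate. There were 3,000 runs per scenario, so the simulation error of a single power figure is about √(0.25 / 3000) = 0.9 points. Power is for 12% v 38% SDF. Arm is in both models, although the article does not name it.

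| Arrest rates (12/30/38%) | OR per SD | Power without | Power with | Variance ratio, standardized risk difference |
|---|---|---|---|---|
| 50/60/77% | 1.0 | 72.5% | 72.5% | 1.014 |
| | 1.5 | 70.2% | 72.2% | 0.968 |
| | 2.0 | 72.0% | 75.9% | 0.934 |
| | 3.0 | 70.3% | 78.0% | 0.843 |
| 55/65/75% | 1.0 | 44.4% | 45.0% | 1.010 |
| | 1.5 | 48.1% | 49.3% | 0.985 |
| | 2.0 | 46.6% | 49.7% | 0.914 |
| | 3.0 | 45.5% | 53.7% | 0.846 |

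For OR 1.5 to 3.0 the power gain runs from 49.3 − 48.1 = 1.2 points to 53.7 − 45.5 = 8.2 points. The variance reduction runs from 1 − 0.985 = 1.5% to 1 − 0.843 = 15.7%. At OR 1.0 there is no real gain and a variance cost of about 1%.

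**5. Scale.** The standard error of the log odds ratio rises with adjustment, for example from 0.515 to 0.552 at OR 2.0 (50/60/77%). The benefit shows in power and in the risk difference. The interval on the logit scale does not get narrower.

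**6. How many terms the data can carry.** With one lesion per child and 55/65/75% arrest, the expected number not arrested is 40 × (0.45 + 0.35 + 0.25) = 42. Two arm terms, two surface terms and one burden term make 5, or 42 / 5 = 8.4 non-arrested lesions per term. Five surfaces coded in full (4 terms), plus size, one CAST term and two arm terms make 8, or 42 / 8 = 5.3. This favours a short list.

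**The case against.** **The list is open.** The article says what the independent variables will include, and it condenses a fuller protocol. A complete covariate set may be in an analysis plan that is not shown. This stands against one tempting inference, that the trial will adjust for habits alone or leave study group out. The text does not say so. It does not remove the point, because the article itself chose which variables to name for its only binary-outcome model, and named neither the treatment nor any examined lesion feature.

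**The model may be a factor analysis.** The habits are collected under Effect Modification, and the model is not called the primary comparison. That may be the intention. If so, the article names no inferential analysis for comparing arms on the primary outcome, and the sentence needs correcting all the more.

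**Eligibility fixes much of what would be adjusted for.** This stands. For the qualifying lesion, size is fixed and CAST severity is narrow, so a gain from adjusting for size cannot be claimed unless further lesions are analysed.

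**The gain is assumed, and validity is not at issue.** This also stands. No prognostic strength is documented, gains are only about 1 to 4 points for odds ratios up to 2.0 per SD, and chance imbalance under randomization is already covered by the type I error rate. A reader might infer bias or an inflated error rate, but nothing in the documents supports that.

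**Conclusion.** The point holds as a specification weakness of moderate weight. The only model named for the binary primary outcome lists parental-questionnaire items and names neither study group nor any baseline lesion or caries measure, although those measures are collected.

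The missing study group matters most, since without it the model answers no treatment question. The covariate choice is an efficiency matter. It is worth about 1 to 8 points of pairwise power and 1.5% to 16% lower variance of the standardized risk difference, assuming odds ratios of 1.5 to 3.0 per SD, the arrest rates shown, 40 children per arm and one lesion each. It is worth nothing if the covariates are not prognostic. The simulation tested one continuous covariate and not the full proposed set, so the range is only a guide.

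Two stronger readings are not supported: that adjusting for lesion size would help when only the qualifying small lesion is analysed, and that adjustment would narrow the confidence interval of the odds ratio.

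**What to change.** Rewrite the model sentence in Statistical Analysis so that the primary 12-month arrest model contains:
- study group, as two indicator terms;
- tooth surface or tooth type, in two or three categories;
- baseline caries burden, as one term (a CAST summary or the number of active lesions);
- lesion size, only if lesions beyond the qualifying small lesion are analysed.

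State the unit of analysis. If several lesions per child are analysed, account for within-child correlation, for example with generalized estimating equations or a random intercept for the child.

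Report the adjusted arm contrasts as the primary result, preferably with a standardized risk difference: average the predicted arrest probability over all children with each group assigned in turn, then subtract. Fix the list before allocation is revealed. Move the questionnaire items to a secondary or exploratory model.

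The cost is the wording and about three covariate terms beside the two arm terms (four if size is included). No new data are needed and the sample size is unchanged. If the analysis plan already specifies such a model, the article's sentence only needs to be brought into line with it.

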### Outcome Measure

The primary outcome measure is caries arrest at the twelfth month of application of SDF. The secondary outcome measure is the caries increment (ie, CAST index).

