### Withdrawal Criteria

During semiannual applications, clinical examination for caries will be done. If any pulpal involvement or abscess is noticed, appropriate treatment will be provided by the principal investigator. The children will be given the right to refuse or withdraw at any point in time.

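### No comparison of 12%, 30% and 38% SDF is specified for the primary outcome: the only model for 12-month arrest does not name treatment group

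*Protocol article*

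**What the plan says.** The protocol article's Objective is to compare three SDF concentrations. Under Outcome Measure: "The primary outcome measure is caries arrest at the twelfth month of application of SDF". The secondary outcome is caries increment on the CAST index.

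Arrest is a yes/no state. Under Baseline and Follow-up Oral Examinations, "a carious lesion is defined as halted when the dentine cannot be penetrated", and otherwise the lesion is active. The Statistical Analysis section keeps that scale: "The dependent variable will be whether the lesion is arrested or not at the 12-month examination". For this logistic model, "the independent variables will include the children’s oral hygiene habits (eg, tooth brushing), fluoride agent use", and the list continues with diet and source of drinking water.

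The same section gives one-way ANOVA to "compare the means of continuous outcome variables if the data follow a normal distribution", with Kruskal-Wallis for skewed data and post hoc tests attached to those two. Categorical variables are to be shown as counts and percentages.

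The Effect Modification section says only this about its method: "A parental questionnaire is administered at baseline regarding the children" and their habits. It lists the same four topics that reappear as the logistic covariates.

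**The concern.** The concentration of SDF is the only thing randomised. A logistic model of arrest on four questionnaire items, with the arms pooled, estimates which habits go with arrest. It gives no estimate for concentration. If no other stated test applies to a binary outcome, the trial's main question has no prespecified estimate or test.

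The rest of the article does not settle the contrast either. The Introduction expects 12% and 30% to be comparable with 38%. Principal Aims in the Discussion expects 38% to be superior, and also describes the aim as finding out whether the lower concentrations are superior. With group unnamed in the model and the direction stated in different ways, both the contrast and its reading are open.

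Effect modification means that the effect of treatment differs by level of a factor. A model without treatment cannot address it.

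**Working it through.** **1. Each stated analysis, checked for a comparison of groups on arrest.**

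| Stated analysis | Outcome it is set out for | Compares groups on 12-month arrest? |
|---|---|---|
| Frequencies and percentages | categorical variables | No, descriptive only |
| One-way ANOVA | means of continuous outcomes | No |
| Kruskal-Wallis | fallback for skewed data | Not assigned to arrest |
| Post hoc tests | follow ANOVA or Kruskal-Wallis | No, tied to those two |
| Binary logistic regression | lesion arrested or not | Right outcome, but group not listed |

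No chi-square test, group term or interaction appears elsewhere in the article.

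**2. Count of contrasts.** Three groups give 3 × 2 / 2 = 3 pairwise contrasts (12% v 38%, 30% v 38%, 12% v 30%). The number specified for the primary outcome is 0 of 3.

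**3. Does Sample Size Estimation supply the missing test?** Inputs from that section: 5% significance, 80% power, effect size 0.63, 3 groups, 20% drop-out. Sidedness and the effect-size metric are not stated; two-sided is assumed here.

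- Two groups, normal approximation: n = 2(1.960 + 0.842)² / 0.63² = 2 × 7.849 / 0.3969 = 39.55, so 40 per group. Then 40 × 3 = 120 and 120 / 0.8 = 150. The article's figures reproduce. The same formula serves a standardised mean difference or Cohen's h for two proportions. The t-test version gives 41.
- Three-group ANOVA with f = 0.63: total N = 28.
- Chi-square test on 2 df with w = 0.63: total N = 25.

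So 120 fits an unadjusted comparison of two groups and neither three-group test at 0.63. Because 0.63 could be a difference in means or in proportions, the section does not identify a test of group on arrest.

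**4. Effect modification.** With three groups, a two-level factor needs two group-by-factor terms. Four such factors would need 4 × 2 = 8 (two-level coding is an assumption). The stated model has none.

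**5. Unit of analysis.** Participant Selection requires at least one qualifying lesion, so a child may contribute several. The dependent variable is worded per lesion. Any group term added to the model must therefore allow for lesions clustered within child, or arrest must be defined once per child.

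**The case against.** Four points can be made for the plan.

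- **The list is open.** It is introduced as what the variables will include, the Objective is a comparison of concentrations, and the sample size is for three groups. The authors may have taken group as understood. This stands as far as it goes: the text shows that group is not named, not that it is excluded. It also does not prespecify the group effect.
- **The logistic model is not called the primary analysis.** That is correct. It may have been meant as a supplementary look at habits. But it is the only analysis with the primary outcome as dependent variable, so on that reading arrest has no between-group analysis at all.
- **Kruskal-Wallis could be used.** Run on 0/1 data it is almost the Pearson chi-square test, and either rank or mean tests could compare a per-child count or proportion of arrested lesions. True, but the article assigns neither test to arrest and defines no per-child summary. A rank test would also give no effect estimate.
- **The detail may sit in an unseen document.** Ethical Considerations refers to a protocol version that is not shown, so a reader who infers that the test will be chosen after seeing the data goes beyond the text. The gap still counts, because the article does not defer the model. It fixes the model, its outcome and its covariates, and the randomised factor is not among them.

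**Conclusion.** The point holds as a fault in what is specified. As written, none of the three randomised contrasts is specified for the primary outcome, and the effect-modification items have no term that could test them. This rests on reading the section as published, not on any assumed rate. It needs correcting because it concerns the trial's only randomised question.

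A reader might go further and infer that the worst failures drop out of the 12-month analysis, because Withdrawal Criteria says: "If any pulpal involvement or abscess is noticed, appropriate treatment will be provided by the principal investigator". The documents do not support that. The section does not say that such children are withdrawn or that their lesions go unscored. Examinations are planned at 6 and 12 months, and CAST has codes for restored teeth (2), pulpal involvement (6), abscess or sinus tract (7) and removal for caries (8). Nor would such losses have a known direction. If arrest were 70% v 50% and 5% of lesions were lost as failures in each arm (all assumed), the observed difference would be 0.20 / 0.95 = 0.211, wider than 0.20; unequal losses could narrow it. No size can be given from the documents.

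**What to change.** Replace the logistic regression text in Statistical Analysis with wording to this effect:

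> Arrest at 12 months (yes/no) will be analysed by logistic regression with randomised SDF group as the main independent variable (38% as reference) and the four sets of questionnaire items as covariates. The contrasts 12% v 38%, 30% v 38% and 12% v 30% will be reported with 95% confidence intervals and [named multiplicity adjustment]. Several lesions in one child will be handled by GEE or cluster-robust standard errors by child [or: arrest will be defined once per child as ...]. Effect modification will be explored by adding group-by-factor interactions.

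Keep ANOVA and Kruskal-Wallis for continuous outcomes, and say which outcomes these are.

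Cost: one paragraph, two extra model parameters for group, and no new data. Intervals widen somewhat. With Bonferroni over three contrasts the normal multiplier rises from 1.960 to 2.394, a ratio of 1.22; a less conservative named procedure would cost less. The widening from clustering cannot be computed, because lesions per child and their correlation are not given. The change should be made before allocation is revealed, which the article places after follow-up is complete.

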### Ethical Considerations

Ethical approval has been obtained from the Institutional Review Board (Ethics Committee II) of Yenepoya (Deemed to be University) for protocol version 3 (YEC2/175). Research aides will serve as contact people and be involved in all phases of the trial. Parents or legal caretakers of the children are given an information sheet outlining the purpose of the study, the specifics of the research, and the processes after the principals consent to participate in the study. Parents are informed of the side effects of the treatment, notably staining of the tooth. Their queries regarding the side effects are addressed. Before beginning this trial, informed consent is obtained. The participants, including the children and their guardians, are free to withdraw at any time during the study. They are also allowed to pursue additional dental care according to their own decisions and financial means.

Caries assessment is done with aseptic precautions and without any harm to the patient. The application of 12% SDF, 30% SDF, or 38% SDF is also done with aseptic precautions and without any harm to the patient. If any complications take place, the child is treated free of charge by the principal investigator.

The study data will be deidentified for privacy and confidentiality protection. No compensation will be offered to the study participants.

The drugs were sponsored by Biodinamica. This drug company has no role in the research.

The Drug Controller General of India does not normally restrict the use of topically applied drugs. Currently, there are also no official guidelines announced for SDF use by dental professional associations or research bodies [10].

